**FIGURE 1 brb370631-fig-0001:**
[figure not shown]
Flow diagram of the study.

The sample size for this study will be calculated using the formula for a superiority trial of two independent sample sizes. Clinical experience and preliminary research indicated an effective rate of 90% in the treatment group and 80% in the control group (Hei et al. 2023, Su et al. 2023, Zhang et al. 2023). Based on these data, we conducted a sample size calculation using a two‐tailed *t*‐test with the following parameters: test boundary value *δ* = 0.15, significance level *α* = 0.025, and power *β* = 0.20 (Zabor et al. 2020). The calculation was performed using the following formula.

$$n=\left[{\left(Z_{\alpha /2}+Z\beta \right)}^{\wedge 2}*\left(p1\left(1-p1\right)+p2\left(1-p2\right)\right)\right]/{\left(\delta -|p1-p2|\right)}^{\wedge 2}$$

Considering a case number ratio of k = 1 between groups, the calculated sample size was 32 cases per group. To account for a potential 10% dropout rate, we increased the sample size to approximately 35 cases per group (International Council for Harmonisation of Technical Requirements for Pharmaceuticals for Human Use 1998). The total sample will be divided into 6 groups: control, EA, HOT, combination therapy, sham therapy, or the healthy, totaling around 210 cases to be included.

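### Section 2.1: the printed sample-size formula with its stated inputs gives 951 (or 785) per group, not 32, and 32 falls far short of the implied 80% power on the plan's own responder-rate basis

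*Protocol article*

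**What the plan says.** In Section 2.1 of the protocol article (the text after Figure 1), the sample size is "calculated using the formula for a superiority trial of two independent sample sizes". The assumed rates are "an effective rate of 90% in the treatment group and 80% in the control group". The calculation is described as a "two‐tailed *t*‐test with the following parameters": "test boundary value *δ* = 0.15", "significance level *α* = 0.025" and "power *β* = 0.20".

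The formula that follows has (Z_α/2 + Z_β)² × [p1(1 − p1) + p2(1 − p2)] in the numerator and (δ − |p1 − p2|)² in the denominator. The result reads: "Considering a case number ratio of k = 1 between groups, the calculated sample size was 32 cases per group". An allowance of 10% for dropout takes this to about 35 per group, and six groups make 210.

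Two other places bear on the point. Section 2.7.1 names the MoCA score as the primary outcome. Section 2.11 plans analysis of variance or the Kruskal–Wallis test and sets the significance level at 0.05, one-tailed.

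**The concern.** The formula, every input and the answer stand in one paragraph, so the answer can be checked without any outside figure. It does not follow. The denominator is the square of a very small quantity (0.15 − 0.10 = 0.05), which must give a large sample, yet a small one is reported.

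The 35 per group and the total of 210 rest on this number. The declared aim is to show that the combination is superior to the single treatments. A reader who takes β = 0.20 at face value will believe that the trial has 80% power for superiority. If it does not, a non-significant result could be misread as evidence of no benefit.

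**Working it through.** **Inputs (all from Section 2.1 unless noted).** p1 = 0.90, p2 = 0.80, |p1 − p2| = 0.10, δ = 0.15, β = 0.20 (Z_β = 0.842), 1:1 allocation. For α = 0.025, Z_α/2 taken literally is 2.241; if 0.025 is read as a one-sided level, Z = 1.960. The one-tailed 0.05 of Section 2.11 gives Z = 1.645.

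Variance term: 0.90 × 0.10 + 0.80 × 0.20 = 0.09 + 0.16 = 0.25.

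**1. Trying to reproduce 32 with the formula as printed.** Denominator: (0.15 − 0.10)² = 0.0025.

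| Z | (Z + 0.842)² | n = (Z + 0.842)² × 0.25 / 0.0025 |
|---|---|---|
| 2.241 | 9.505 | 950.5, so 951 |
| 1.960 | 7.849 | 784.9, so 785 |
| 1.645 | 6.183 | 618.3, so 619 |

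No reading of α comes near 32.

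**2. What does give 32.** With a plus sign the denominator is (0.15 + 0.10)² = 0.0625.

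- Z = 1.960: 7.849 × 0.25 / 0.0625 = 31.4, so 32.
- Z = 2.241: 9.505 × 0.25 / 0.0625 = 38.02, so 39.

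The first line is the calculation for non-inferiority with a 15-point margin when the new treatment is assumed to be 10 points better. The second shows that, even with this sign, the stated two-tailed 0.025 does not give 32.

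There is a second route. If the phrase about power and β is read literally as 20% power (Z_β = −0.842) and δ is dropped, then with Z = 1.960: (1.960 − 0.842)² × 0.25 / 0.10² = 31.3, so 32. That would be a superiority calculation with 20% power.

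**3. Power for superiority at the plan's own rates.** The standard error of the difference is √(0.25 / n), and power is Φ(0.10 / SE − Z).

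- n = 32: SE = 0.0884, 0.10 / SE = 1.131.
- n = 35: SE = 0.0845, 0.10 / SE = 1.183.

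| Level | Power, n = 32 | Power, n = 35 |
|---|---|---|
| two-sided 0.025 (Z = 2.241) | Φ(−1.110) = 13% | 14% |
| two-sided 0.05 (Z = 1.960) | Φ(−0.829) = 20% | 22% |
| one-tailed 0.05 (Z = 1.645) | Φ(−0.514) = 30% | 32% |

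Exact enumeration of the chi-square test at n = 32 gives 13.4% and 20.5% for the two two-sided levels. Fisher's test gives less, 6.7% and 10.9%.

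**4. Scale of an ordinary superiority comparison.** With no margin, 80% power for 90% against 80% needs 7.849 × 0.25 / 0.01 = 196.2, so 197 per group, at two-sided 0.05. At two-sided 0.025 it needs 9.505 × 0.25 / 0.01 = 237.6, so 238. A pooled-variance version gives 199 and 242.

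**The case against.** The minus sign may be a typesetting slip, with the calculation otherwise done as intended. That does not repair the paragraph. With a plus sign the formula is one for non-inferiority, while the text says superiority, and the stated two-tailed 0.025 then gives 39.

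The more substantial objection is that the trial will not test a responder rate. Its primary outcome is the MoCA score, analysed on a continuous scale or by ranks, and the article gives no MoCA standard deviation or expected difference. This objection stands and limits the point. A reader might infer that the MoCA comparison has only 13% to 30% power, that a negative trial is to be expected, or that the size supports nothing but non-inferiority. The article supports none of these: power for MoCA could be higher or lower and is simply not established.

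Two further inferences should be resisted. One is that 32 can have come only from a non-inferiority formula; the second route in the working also gives 32, so the plus sign is a consistent explanation and not a proven one. The other is that the trial needs 785 or 951 per group. The assumed difference (0.10) is below δ (0.15), so superiority by that margin could not be shown under the plan's own assumptions, and the printed formula is itself mis-specified.

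Finally, the article never prints 80% power as such. It is the natural reading of β = 0.20. The Discussion does concede a relatively small sample, but it does not say that the stated calculation fails.

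**Conclusion.** The point holds. The stated 32 per group does not follow from the printed formula and inputs, which give 951, or 785 with Z = 1.96: about 30 and 25 times the stated figure (951 / 32 = 29.7; 785 / 32 = 24.5). The figure 32 is consistent with a non-inferiority sign and Z = 1.96, which contradicts the stated superiority hypothesis and does not match the stated two-tailed α.

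On the responder-rate basis chosen for sizing, 32 evaluable per group gives about 13% to 30% power for superiority, depending on which of the article's significance levels is used. The implied 80% is not supported under any of them. The power figures rest on the article's 90% and 80%, on a two-group comparison of proportions, and on the normal approximation. They say nothing about power for the MoCA score.

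**What to change.** Rewrite the sample-size paragraph of Section 2.1 so that it:

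- shows the formula, sign, α (with its sidedness) and hypothesis that actually produced 32;
- withdraws the implied 80% power for superiority and labels β correctly;
- states that 32 evaluable per group has about 13% (two-sided 0.025), 20% (two-sided 0.05) or 30% (one-tailed 0.05) power for 90% against 80%, and that this applies only to the responder basis;
- says that power for the MoCA comparison has not been established;
- commits to reporting effects with confidence intervals, so that a non-significant result is not read as no benefit.

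Do not put 785 or 951 in place of 32, for the reason given under the objection. The cost is one rewritten paragraph and a less favourable stated power. No extra patients or procedures are needed.

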#### Primary Outcomes

2.7.1

Participants' cognitive abilities will be assessed at three‐time points: baseline (week 0), during treatment (week 4), and follow‐up (week 8) (Table 2). The primary outcome measures include the Montreal Cognitive Assessment (MoCA), which are commonly used tools for evaluating cognitive function across different types of impairment.

**TABLE 2 brb370631-tbl-0002:** Schedule of enrollment, intervention, and assessment.

	Week 0 (baseline)	Week 4	Week 8
MMSE	X	X	X
MoCA	X	X	X
MBI	X	X	X
TCD	X	X	
fNIRS	X	X	
fMRI	X	X	
STAI	X	X	
Adverse Effects			

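### The printed superiority formula does not give 32 per group; 32 matches a non-inferiority calculation, and no power is stated for the MoCA score

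*Protocol article*

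**What the plan says.** Section 2.1 of the protocol article (the paragraph after Figure 1) says that the size is "calculated using the formula for a superiority trial of two independent sample sizes". It gives these inputs:

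- Rates: "Clinical experience and preliminary research indicated an effective rate of 90% in the treatment group and 80% in the control group".
- Margin: "test boundary value *δ* = 0.15".
- Test and error rates: a "two‐tailed *t*‐test with the following parameters", "significance level *α* = 0.025", and a value of 0.20 labelled as power but given the symbol β.
- Allocation ratio: 1.

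The printed formula has (Z for α/2 plus Z for β) squared, times p1(1−p1) + p2(1−p2), over (δ − |p1 − p2|) squared. The result is that "the calculated sample size was 32 cases per group", raised to about 35 for 10% dropout and to about 210 over six groups.

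Three other places bear on this. The Aims in the Abstract and the end of the Introduction set out to show that the combination is superior to either single treatment. Section 2.7.1 says: "The primary outcome measures include the Montreal Cognitive Assessment (MoCA"). Section 2.11 tests at 0.05 one-tailed and names analysis of variance, repeated-measures analysis of variance and Kruskal–Wallis.

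**The concern.** This paragraph is the only justification in the article for 35 per arm. A reader who puts the stated inputs into the stated formula gets a number some twenty to thirty times larger than 32, so either the formula, an input or the result is wrong.

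The hypothesis itself is also in doubt. A margin of 0.15 together with an expected difference of 0.10 makes sense for non-inferiority but not for superiority by that margin, and the trial's aim is superiority.

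Finally, the calculation concerns a proportion, described as a t-test, whereas the primary outcome is a scale score analysed by methods for continuous data. If the paragraph stands, readers will credit the trial with 80% power to show superiority on its primary outcome, and the article supports neither part of that.

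**Working it through.** **Inputs (all from section 2.1 unless noted).** p1 = 0.90, p2 = 0.80, so |p1 − p2| = 0.10 and V = 0.9 × 0.1 + 0.8 × 0.2 = 0.25. δ = 0.15. β = 0.20, read as 80% power, so Z for β is 0.8416. Alpha has three possible readings:

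- 0.025 as a single tail: Z = 1.960
- two-tailed 0.025, as the formula's α/2 literally requires: Z = 2.2414
- one-tailed 0.05, from section 2.11: Z = 1.645

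**Step 1. The printed formula.** The denominator is (0.15 − 0.10)² = 0.0025.

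- Z = 1.960: (1.960 + 0.8416)² = 7.849; 7.849 × 0.25 / 0.0025 = 784.9, so 785
- Z = 2.2414: (2.2414 + 0.8416)² = 9.505; 9.505 × 0.25 / 0.0025 = 950.5, so 951
- Z = 1.645: 6.183 × 0.25 / 0.0025 = 618.3, so about 618

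The stated 32 is not reproduced under any reading.

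**Step 2. What does reproduce 32.** Adding the margin gives a denominator of (0.15 + 0.10)² = 0.0625. With Z = 1.960, 7.849 × 0.25 / 0.0625 = 31.4, so 32. This is the standard non-inferiority calculation with a 15-point margin and one-sided 0.025. Its power at 32 per group is Φ(0.25/0.0884 − 1.960) = 81%, where the standard error is √(0.25/32) = 0.0884. With Z = 2.2414 the same form gives 39.

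A second route exists. With no margin, and 0.20 taken literally as 20% power, (1.960 − 0.8416)² × 0.25 / 0.10² = 31.3, also 32.

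**Step 3. Superiority by the stated margin.** The assumed difference is 0.10 − 0.15 = −0.05 relative to the boundary, on the wrong side of it. Squaring removes the sign, so the formula still returns a number. Power to exceed the margin at 32 per group is Φ(−0.05/0.0884 − 1.960) = 0.6%, and a larger sample does not help.

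**Step 4. Plain superiority (no margin), 90% against 80%.** Power at 32 per group is Φ(0.10/0.0884 − Z) = Φ(1.131 − Z). The size in the last column uses the pooled-variance formula for 80% power.

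| Test level | Power at 32 per group | Needed per group for 80% |
|---|---|---|
| two-sided 0.05 | 20% | 199 |
| two-sided 0.025 | 13% | 242 |
| one-sided 0.05 | 30% | 157 |

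The unpooled formula at two-sided 0.05 gives 7.849 × 0.25 / 0.01 = 196.2, so 197. An exact binomial calculation of the chi-square test at 32 per group also gives 20% power at two-sided 0.05. At 35 per group, power at that level is 21–22%.

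**Step 5. What the size gives on MoCA.** For an unadjusted two-sample t-test with 32 evaluable per arm and 80% power, the detectable difference is 0.71 SD (two-sided 0.05), 0.79 SD (two-sided 0.025) or 0.63 SD (one-sided 0.05).

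**The case against.** The article does not say how 32 was obtained. It is tempting to conclude that it can only have come from adding the margin, but the second route in the working also gives 32, and so does the printed formula if δ was meant as −0.15 and the sign was lost. The non-inferiority route is the most plausible because a margin is stated. The lost-sign route is also non-inferiority, and the 20%-power route would itself mean 20% power. None of them rescues a superiority claim at 80% power.

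A reader might also take 785 as the size the trial should have had. The documents do not support that, since the hypothesis behind the printed formula cannot hold under the assumed rates.

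A reader might infer that a null MoCA result would come from a trial with a one-in-five chance of success. That does not follow. The 20% belongs to a comparison of proportions that section 2.11 does not plan, and power on MoCA cannot be derived from the article. The supportable statement is that none is given.

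Lastly, this is a condensed article, and a responder definition may exist in a full protocol. So the point is not that the effective rate is undefined everywhere. It is that the sample size rests on a proportion while the named primary outcome is a score. The 80% figure is itself a reading of the value 0.20, though the natural one.

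**Conclusion.** The concern holds in this form. The stated 32 per group does not follow from the superiority formula and inputs printed beside it under any of the three alpha readings; the formula returns roughly 618 to 951. The figure is most plausibly a non-inferiority size, which does not match the superiority aim in the Abstract and Introduction. For plain superiority on the assumed rates, power at 32 per group is 13% to 30% depending on alpha and sidedness, against the 80% implied by β = 0.20. That spread arises because sections 2.1 and 2.11 disagree on the level and the number of tails.

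The calculation also says nothing about MoCA, so the trial has no stated power for its primary outcome. These figures rest on the article's own rates, normal-approximation formulas and 32 evaluable per arm. The MoCA figures assume a single unadjusted two-arm comparison. Expressing them in points would need an SD that the article does not give.

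**What to change.** Keep 35 per arm and rewrite the paragraph:

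1. Remove the printed formula and the claim that the size comes from a superiority calculation.
2. State one hypothesis, and one alpha with its sidedness, the same in sections 2.1 and 2.11.
3. Name the comparison and the time point for MoCA. Section 2.7.1 lists weeks 4 and 8 without choosing between them, and the aim involves the combination against each single treatment.
4. State what the fixed size delivers. For example, 32 evaluable per arm give 80% power, in an unadjusted two-arm comparison of MoCA, for a difference of 0.71 SD at two-sided 0.05 (0.79 SD at two-sided 0.025, 0.63 SD at one-sided 0.05). Use the figure for the level chosen in item 2.
5. If non-inferiority was intended, say so, correct the sign in the formula, and limit the conclusion to non-inferiority.

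The reason for choosing 35 should come from the investigators; the article offers none apart from this calculation. The cost is one rewritten paragraph and a less favourable power statement. No extra patients are needed.

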### Inclusion Criteria

2.2

Stroke as per the Traditional Chinese Medicine (TCM) definition, presenting symptoms include unilateral paresis or paralysis, sensory deficits, speech impairment, and hemianopsia. PSCI diagnosis involves clinically significant deficits in at least one cognitive domain and severe disruption of instrumental ADLs/ADLs.The scores on the MMSE scale must adhere to the following criteria: Less than 17 points for individuals with illiteracy, less than 20 points for those with primary school education, and less than 24 points for individuals with a middle school education or higher.The age range is 45 to 70 years;No history of mental illness, clear consciousness, stable vital signs, and able to complete the scale assessment;Within 3–6 months post‐stroke, diagnosed as a patient in the recovery period of cerebral infarction (or cerebral hemorrhage) at admission;Signed informed consent by the patient or their family.

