#### Secondary Outcomes

2.7.2

The mini‐mental state examination (MMSE): MMSE score will be assessed at three‐time points: baseline (week 0), during treatment (week 4), and follow‐up (week 8).The Modified Barthel Index (MBI): MBI scores will be utilized to evaluate patients' activities of daily living and their level of dependency. It will be assessed at three‐time points: baseline (week 0), during treatment (week 4), and follow‐up (week 8).Transcranial Doppler (TCD)

TCD involves the following steps: First, prepare the equipment, including the transcranial Doppler ultrasound device and the probe, ensuring that the device is properly calibrated and the appropriate parameters are set. Second, prepare the patient or subject, who is typically placed in a supine or sitting position, with ultrasound coupling gel applied to the scalp to ensure sound wave conduction, and the detection points are marked. Finally, detect the cerebral vessels by selecting the appropriate detection window (such as the temporal window, occipital window, and ophthalmic artery window), and adjust the probe angle and position to locate the target cerebral vessels.

Parameter settings: The light source wavelength typically employed ranges from near‐infrared light of 650 to 900 nm, as this range exhibits low absorption of light by both hemoglobin and water. The light source can be either a pulsed laser or an ultra‐short pulsed laser. Detection is performed using a Time‐Correlated Single Photon Counting (TCSPC) detector, which allows for time resolution at the picosecond (ps) level to measure the time of flight of photons. The probe layout generally maintains a distance of 2 to 4 cm between the light source and the detector.

Analysis method: Temporal point spread function (TPSF): This method involves analyzing the time‐of‐flight distribution of photons to derive the optical characteristics of tissue, specifically the absorption coefficient and scattering coefficient. Differential Pathlength Factor (DPF): This factor is employed to correct the path length of photons traveling through tissue. Calculation of Hemoglobin Concentration: The concentration changes of oxygenated hemoglobin (HbO2) and deoxygenated hemoglobin (HbR) are calculated based on variations in the absorption spectrum.
4Near‐infrared spectroscopy (fNIRS)

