### Data Analysis

2.11

Researchers who are blind to the groupings will conduct data management and statistical analysis on the data acquired using the statistical software SPSS 22.0 (SPSS Inc., Chicago, IL, United States). Descriptive statistics will be utilized to depict the baseline characteristics of the two participant groups, with mean ± standard deviation for normally distributed continuous data and median and quartiles for non‐normally distributed continuous data. The normality of the data will be assessed using the Shapiro–Wilk test, and the homogeneity of variance will be assessed using the Levene test. One‐way analysis of variance (ANOVA) will be used for comparisons among multiple groups for normally distributed continuous data, while repeated measures analysis of variance will be used for within‐group pre‐ and post‐treatment comparisons. The Kruskal–Wallis test will be employed for non‐normally distributed continuous data. The significance level (α) for the statistical hypothesis tests will be set at *p* < 0.05, one‐tailed.

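### The qualifying MMSE appears to double as baseline; if it does, regression to the mean biases the within-group pre/post MMSE test towards improvement

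*Protocol article*

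**What the plan says.** Four statements in the protocol article bear on this.

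- **Entry (2.2 Inclusion Criteria).** "The scores on the MMSE scale must adhere to the following criteria: Less than 17 points for individuals with illiteracy", then "less than 20 points for those with primary school education, and less than 24 points for individuals with a middle school education or higher". No time is given for this measurement.
- **Outcome (2.7.2 Secondary Outcomes).** "MMSE score will be assessed at three‐time points: baseline (week 0), during treatment (week 4), and follow‐up (week 8").
- **Schedule (Table 2 in 2.7.1).** The table covers enrolment, intervention and assessment. Its only pre-treatment column is week 0, and it has no screening column.
- **Analysis (2.11 Data Analysis).** "repeated measures analysis of variance will be used for within‐group pre‐ and post‐treatment comparisons". One-way ANOVA "will be used for comparisons among multiple groups for normally distributed continuous data". "The significance level (α) for the statistical hypothesis tests will be set at" p < 0.05, one-tailed.

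The article does not mention regression to the mean or a second pre-treatment MMSE, and it does not say how a within-group change may be interpreted.

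**The concern.** An MMSE score is true ability plus error on the day. Selecting patients below a limit lets in some whose score was low by chance and keeps out others whose score was high by chance. Among those admitted, the error in the qualifying score is negative on average. If that score is also the pre-treatment value, the mean of the repeat score is expected to rise with no treatment effect, in all five patient arms, control and sham included.

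The within-group test then has a false-positive rate above the stated 5%. Because significance is judged arm by arm, chance will often make some arms significant and others not. The trial's stated aim is superiority of the combination over single treatments, and such a pattern is easily misread as support for it.

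**Working it through.** The plan states no figure on this point, so there is none to reproduce. The question is how large the bias could be.

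**Inputs from the article:** cut-offs 17, 20 and 24 (2.2); 35 per group (2.4); one-tailed 0.05 (2.11).

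**Assumed, because the article does not give them:** MMSE in the screened population normal with mean μ of 16 to 26, SD 4 to 5, retest reliability ρ of 0.80 to 0.90; no true change; the qualifying score is the baseline. Cut-off 24 is used. The result depends on the distance from mean to cut-off, so the lower limits behave alike at correspondingly lower means.

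**Expected spurious gain:** (1 − ρ) × SD × φ(a)/Φ(a), with a = (23.5 − μ)/SD. Here φ and Φ are the standard normal density and distribution function, and 23.5 is the continuity-corrected limit for a score below 24.

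**Worked example: μ = 22, SD = 5, ρ = 0.80**

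- a = (23.5 − 22)/5 = 0.30; φ(a)/Φ(a) = 0.3814/0.6179 = 0.617.
- Gain = 0.20 × 5 × 0.617 = 0.62 points.
- The SD of the change among those selected is about 3.07 (simulated), so the standard error is 3.07/√35 = 0.52.
- The statistic centres on 0.62/0.52 ≈ 1.19, against a one-tailed critical value of 1.69 (34 df).
- Chance of a significant rise ≈ Φ(1.19 − 1.69) = Φ(−0.50) ≈ 31%, and simulation agrees.

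**Range.** Simulated groups of 35, paired t-test as the two-time-point form of the repeated-measures test; low and high over SD 4 to 5 and ρ 0.80 to 0.90:

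| Source mean | Spurious gain (points) | One-tailed 0.05 | Two-tailed 0.05 |
|---|---|---|---|
| 16 | 0.03–0.14 | 6–8% | 5–6% |
| 18 | 0.07–0.25 | 8–12% | 5–8% |
| 20 | 0.13–0.41 | 11–19% | 7–12% |
| 22 | 0.23–0.62 | 19–31% | 12–21% |
| 24 | 0.35–0.86 | 31–51% | 20–38% |
| 26 | 0.49–1.14 | 45–76% | 32–64% |

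With scores rounded to whole points and bounded at 0 and 30, the largest gain is 1.16, hence about 1.2.

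**Split results.** If each of the three active arms (EA, HOT, combination) is falsely significant with probability p, at least one is significant and at least one is not with probability 1 − p³ − (1 − p)³. This is 14% at p = 0.05, 17% at p = 0.06, 75% at p = 0.50 and 55% at p = 0.76.

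**What is not affected.** For means 20 to 26 and reliability 0.70 to 0.95, the two-sided 0.05 comparison of change between two randomised patient arms kept an error rate of about 4% to 6%, even with the qualifying score as baseline. With a fresh MMSE as baseline after the qualifying one, the one-tailed within-group rate was also about 4% to 6%.

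**The case against.** **The premise is inferred.** No sentence says that the qualifying MMSE is the week-0 value. Table 2 shows no consent or randomisation step either, its adverse-effects row is blank, and a condensed article may omit a screening visit that the full protocol contains. This stands, and it makes the point conditional. One sentence in the article would settle it.

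**The size rests on assumptions.** Section 2.2 also requires a PSCI diagnosis with severe disruption of daily activities, so a low source mean is plausible. At means of 16 to 20 the one-tailed rate is only about 6% to 19%. A repeated-measures F test has no direction, so the two-tailed column may be nearer to what is run, and three MMSE time points are planned where the check uses two. All this stands. The direction of the bias does not depend on it.

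**The article attaches no efficacy claim to the within-group test.** True, but it does not call the test descriptive either, and it applies the same significance level.

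**Within-arm change is uninterpretable anyway.** Every patient receives four weeks of cognitive training and is 3 to 6 months after stroke, in the recovery period. A rise could not be credited to EA or HOT even with a clean baseline. This stands. It supports removing the test as evidence of efficacy and means that a second baseline MMSE alone is not a full remedy.

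**A stronger reading to avoid.** A reader might infer that the trial's main comparison is compromised, or that the test will show improvement in each arm. The documents do not support this. The aim is a between-arm question, and the shift is equal in expectation across randomised patient arms. The primary MoCA is not the entry scale; it would be touched only so far as its error on the day correlates with that of the MMSE. The bias raises the chance of a significant rise; it does not guarantee one.

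**Conclusion.** The point holds conditionally. If the qualifying MMSE is the week-0 value, as Table 2 suggests without stating it, the within-group pre/post MMSE test is biased upward in every patient arm. With no true change, cut-off 24, n = 35, SD 4 to 5 and reliability 0.80 to 0.90, the spurious gain is about 0.03 to 1.2 points and the one-tailed error rate about 6% to 76%. The assumed source mean is the main driver. The article supplies none of these parameters, so the range cannot be narrowed from it.

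The harm is confined to a secondary, within-arm test. Comparisons among the randomised patient arms are sound on this point. Comparison of MMSE change with the healthy group is not protected, because that group is not selected for a low score.

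**What to change.** In section 2.11, remove the within-group pre/post MMSE test as evidence of efficacy and report within-arm MMSE change descriptively only. Base MMSE conclusions on differences between the randomised patient arms at weeks 4 and 8, adjusted for week-0 MMSE, and leave the healthy group out of that comparison.

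State in section 2.2 or Table 2 whether the eligibility MMSE is the week-0 score. Optionally, if a separate admission or screening MMSE exists, use it for eligibility only, take week 0 as the baseline, and keep patients whose week-0 score is no longer below the limit.

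The main change is a few words of text and needs no extra data. A separate screening MMSE, if not already taken, adds one short assessment per patient. The downside is that within-arm gains can no longer be claimed as benefit.
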